**Secondary Objective:**

The secondary objectives of this study are as follows:

- To test the hypothesis that PEA-LUT will slow the rate of decline associated with FTD in the activities of daily living, as assessed with the Alzheimer's disease Cooperative Study Activities of Daily Living (ADCS-ADL), using a GLMM for repeated measures.
- To assess benefit of treatment with PEA-LUT on frontal cognitive functions, as demonstrated through the Frontal assessment battery (FAB), using a GLMM for repeated measures.
- To evaluate efficacy of treatment with PEA-LUT on behavior, as demonstrated through the Neuropsychiatric Inventory (NPI) and Frontal Behavioral Inventory (FBI), using a GLMM for repeated measures.
- To evaluate efficacy of treatment with PEA-LUT on language function, as demonstrated through the Screening for Aphasia in Neurodegeneration (SAND) using a GLMM for repeated measures.
- To evaluate efficacy of treatment with PEA-LUT on global cognition, as demonstrated through the Addenbrooke's Cognitive Examination Revised (ACE-R) and Mini Mental State Examination (MMSE) using a GLMM for repeated measures.
- To evaluate changes from Baseline to Week 24 in the TMS/EEG protocol, to evaluate effects of PEA-LUT on DLPFC cortical activity, oscillatory activity and connectivity.
- Nature, frequency and severity of adverse events (AEs): to assess the safety and tolerability of PEA-LUT given for up to 24 Weeks.

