**6)** Global Cognition [Time Frame: change from baseline to week 24]: Addenbrooke's Cognitive Examination Revised (ACE-R)The scores range from 0-100 with a higher score meaning less cognitive impairment.

**7)** Global Cognition [Time Frame: change from baseline to week 24]: Mini Mental State Examination (MMSE). The scores range from 0-30 with a higher score meaning less cognitive impairment.

**8)** TMS-evoked EEG responses, in terms of potentials (i.e., TEPs) and oscillations (i.e., TRSP) as a novel probe of cortical excitability changes induced by PEA-LUT. TEPs and TRSP will be computed by stimulating the left and right DLPFC and simultaneous electroencephalography recordings over all the scalp.

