**2.3.4. Analysis of Efficacy Outcomes**

Normality assumption of end-points variables will be assessed by inspection of the distribution plots and by Kolmogorov-Smirnov and Shapiro-Wilk tests. Preliminary descriptive analyses will be performed by means, frequencies, standard deviations (SD) and percentages. Comparison of socio-demographic and clinical features between the study groups at baseline will be performed through t-test or Mann-Whitney tests. The longitudinal assessment of the end-points across groups will be performed through Generalized Linear Mixed Model (GLMM) for repeated measures with random intercept and random slope to account for individual differences at baseline as well as for individual change after the treatment. GLMMs will be applied to FTLD-CDR SoB and the other efficacy outcome measures, MMSE, ACE-R, FBI, SAND, ADCS-ADL, FAB and NPI, as dependent variables (one model for each outcome measure), and group, time and group x time interaction as independent factors. In detail, analysis of residuals (after adjustment for variables that mainly affect the outcomes: age and education) led us to adopt GLMMs for Gaussian data with identity link function for FTLD-CDR SoB, SAND, FBI, ACE-R, MMSE, ADCS-ADL and FAB; whereas GLMM for Negative binomial data, with log-link function, will be used for NPI. The GLMMs on MMSE and FAB will be adjusted for age and education.

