TEPs analysis will be conducted in two steps. First, to identify the exact the TEP time windows at which there will be a significant difference, we will perform multiple t-tests (corrected with false discovery rate method) at each time point of the TEP waveform from -100 to 300 ms after TMS. This analysis will be conducted for each group (PEA-LUT group vs placebo) and for each evaluation (baseline W0 vs W24). Once detected the significant time windows, we will compare the mean TMS-evoked activity (dependent variable) within these intervals with a generalized linear mixed model (GLMM -for Gaussian data-) for repeated measures with group (real vs. sham), time (W0 vs. W24) and “window” as independent factors. TRSP analysis will be conducted with dependent t-tests comparing the different frequency bands (alpha, beta, gamma, theta) in the two time points of evaluation (W0 and W24). Safety analyses for the treatment period will include comparisons between PEA-LUT group and placebo groups by 2-sided 0.05 significance level Chi-square tests. Statistical analyses will be performed with IBM SPSS statistics, version 24.0 and R software; significance alpha level test is set up at 0.05.

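### The SAP states only paired baseline-versus-week-24 t-tests for TMS-evoked oscillations (TRSP) and no PEA-LUT versus placebo comparison, so the analysis as written cannot show a treatment effect on that outcome

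*Combined protocol and SAP*

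**What the plan says.** Section 1.5 (Secondary Objective) sets out to evaluate baseline-to-week-24 changes in the TMS/EEG protocol, and gives the purpose as "to evaluate effects of PEA-LUT on DLPFC cortical activity, oscillatory activity and connectivity". Section 1.9 (Secondary Efficacy Measures, item 8) lists TEPs and TRSP together and describes them "as a novel probe of cortical excitability changes induced by PEA-LUT".

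SAP section 2.3.4 then treats three kinds of outcome differently:

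- **Clinical scales.** "GLMMs will be applied to FTLD-CDR SoB and the other efficacy outcome measures, MMSE, ACE-R, FBI, SAND, ADCS-ADL, FAB and NPI" are the dependent variables, with group, time and the group-by-time interaction as factors.
- **TEPs.** After a screening step with FDR-corrected t-tests, a Gaussian mixed model is planned "for repeated measures with group (real vs. sham), time (W0 vs. W24) and “window” as independent factors". No interaction is named.
- **TRSP.** The whole specification is: "TRSP analysis will be conducted with dependent t-tests comparing the different frequency bands (alpha, beta, gamma, theta) in the two time points". Those points are baseline and week 24. No group factor, no contrast between arms and no multiplicity rule is given. The plan does not say whether the tests are run within each arm or on all patients together, or separately for the left and right DLPFC.

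**The concern.** A dependent t-test of W0 against W24 estimates within-patient change. In a 24-week trial in a progressive disease, that change can include disease course, differences between recording sessions, regression to the mean and any placebo response as well as a drug effect. Only comparison with the randomised placebo arm removes the shared part, and the stated TRSP test does not use that arm as a control.

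The question matters because the rationale (section 1.4) already reports increased beta and gamma oscillations after one month of PEA-LUT, in a pilot of 18 patients described only as before versus after treatment. The randomised trial could put a control on that finding. Followed to the letter, the SAP would repeat the uncontrolled comparison over a longer period.

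**Working it through.** **1. The plan's own figure.** The SAP gives no sample-size figure for TRSP. Its only one (section 2.1) is 18 per group, from effect size 0.93, a two-tailed paired Wilcoxon test, alpha 0.05 and power 0.95. Taking 0.93 as the mean change in SDs of change, paired-t power is P(|T| > t(0.975, n−1)), with T noncentral t and noncentrality 0.93·√n. At n = 18 this gives 0.960. With the Wilcoxon efficiency of 3/π it gives 0.951, and a simulated Wilcoxon test gives 0.936 at n = 17 and 0.954 at n = 18. So 18 reproduces. The planning basis is itself a paired, within-group one.

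**2. Paired tests when the drug does nothing.** Inputs from the documents: 25 and 23 patients (section 2.1) and two-sided alpha 0.05 (section 2.3.1). Assumed, because the documents give no value: both arms share the same change c, in SDs of change, from 0.3 to 0.5, with no drop-outs. The noncentrality is c·√n; critical values are 2.064 (n = 25), 2.074 (n = 23) and 2.012 (n = 48).

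| c | PEA-LUT significant (n = 25) | Placebo significant (n = 23) | PEA-LUT significant, placebo not | Pooled significant (n = 48) |
|---|---|---|---|---|
| 0.3 | 0.302 | 0.280 | 0.302 × 0.720 = 0.217 | 0.530 |
| 0.4 | 0.484 | 0.450 | 0.484 × 0.550 = 0.266 | 0.775 |
| 0.5 | 0.670 | 0.630 | 0.670 × 0.370 = 0.248 | 0.924 |

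None of these is a 5% error rate for a treatment effect. The discordant pattern depends on c: it is 0.048 at c = 0 and 0.043 at c = 0.8, where both arms are nearly always significant. The PEA-LUT test alone is then significant in 97% of trials.

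**3. Several measures.** Four bands tested once each give 1 − 0.95^4 = 0.185 for at least one false positive when nothing changes; eight tests give 1 − 0.95^8 = 0.337. Both assume independent tests.

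**4. The between-arm test.** For the W24−W0 change, 25 versus 23, the noncentrality is d/√(1/25 + 1/23) = 3.461·d on 46 degrees of freedom, critical value 2.013. The type I error is 5% whatever change the arms share.

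- d = 0.5: noncentrality 1.731, power 0.395
- d = 0.8: noncentrality 2.769, power 0.774
- d = 0.93: noncentrality 3.219, power 0.883
- 80% power needs d of about 0.83

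Under Bonferroni over eight tests (alpha 0.05/8 = 0.00625, critical value 2.866), power at d = 0.8 falls to 0.469, and 80% power needs d of about 1.08.

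**The case against.** The best defence is the general sentence in section 2.3.4: "The longitudinal assessment of the end-points across groups will be performed through Generalized Linear Mixed Model (GLMM"). TRSP is a secondary end-point, so it could be said to be covered. That reading is weak. The text goes on to name eight clinical scales without TRSP, and gives TRSP its own method immediately after a TEP model that does include group.

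A second defence has some force. The TMS/EEG objective opens with change from baseline to week 24 and, unlike the clinical-scale objectives, promises no mixed model. The paired test does match that opening. It does not match the stated purpose, the effect of PEA-LUT.

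Several stronger readings are tempting but unsupported:

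- **That the plan will treat significance in PEA-LUT but not in placebo as an effect.** It never says so. The risk is that it leaves a reader nothing better.
- **That there are 16 uncorrected tests, with a 56% chance of a false positive.** The product 4 bands × 2 sides × 2 arms = 16 gives 1 − 0.95^16 = 0.56, but the plan does not state that layout, and the count includes placebo-arm results that nobody would claim as a drug effect.
- **That the misleading pattern is almost certain in at least one of eight band-by-side measures.** With independent measures the figures are 86%, 92% and 90% at c = 0.3, 0.4 and 0.5. But all eight measures come from the same patients, and the figures need an equal change in every one. Simulation (40,000 runs, 25 and 23 patients) gives 64%, 72% and 69% with a correlation of 0.5 between measures, and 54%, 61% and 59% with 0.7. These correlations are also assumptions.
- **That the trial's mechanistic evidence as a whole is uncontrolled.** TEPs share that role, and their model has a group factor.

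**Conclusion.** The gap is real and rests on the text, not on the illustration: for TRSP the SAP states no comparison of PEA-LUT with placebo, and no result of the stated tests could establish a treatment effect. If both arms shift by an assumed 0.3 to 0.5 SD with no drug effect, a significant PEA-LUT paired test arises in 30% to 67% of trials. The discordant pattern arises in 22% to 27% per measure, and a significant pooled test in 53% to 92%.

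The scope is narrow. TRSP is part of the last of eight secondary efficacy measures. The primary FTLD-CDR SoB and the seven other clinical scales have an explicit group-by-time term and are untouched. This should be fixed; it does not undermine the trial's main efficacy analysis. The missing multiplicity rule for TRSP is a lesser and more debatable matter in a phase IIa secondary measure.

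**What to change.** For each frequency band and each stimulated side, make a between-arm test the main TRSP analysis. Two forms would serve:

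- a Gaussian mixed model with group, time and an explicit group-by-time term, as section 2.3.4 specifies for the clinical scales; or
- week-24 power compared between arms with adjustment for baseline power.

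Do not simply copy the TEP model: as written it names group, time and window but no interaction, so its main effects need not isolate the treatment effect.

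Report the arm difference with a 95% confidence interval, and keep the paired tests as description of change within each arm. Then either apply FDR across the band-by-side tests or label them exploratory.

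The cost is SAP wording and one model per band and side (4 × 2 = 8). Both recordings are already scheduled at baseline and week 24. The real drawback is precision: unadjusted power is about 40%, 77% and 88% for differences of 0.5, 0.8 and 0.93 SD of change, and about 47% at 0.8 SD under Bonferroni over eight tests. The SAP should say so, so that a non-significant result is not read as absence of effect.

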In the current project, we hypothesize that the administration of ultra-micronized PEA-LUT may have a clinical impact in FTD patients. In particular, PEA-LUT treatment could be able to reduce disease severity progression in FTD, with a related improvement of daily living activities of affected people. Potentially the proposed project could provide a valid treatment for cognitive and behavioural dysfunction in FTD patients, with consistent impact for the National Health Systems and minimum cost for the patients. Moreover, the application of recent neurophysiological tools, such as the combined use of transcranial magnetic stimulation (TMS) during electroencephalography (EEG) will allow us to understand how the administration of PEA-LUT may modulate the cortical activity of the dorsolateral prefrontal cortex in FTD patients, defining the neurophysiological biomarkers of clinical improvement.

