**2.3 Statistical and Analytical Plans**

**2.3.1. General Considerations**

Unless otherwise noted, all tests of treatment effects will be conducted at a 2-sided alpha level of 0.05; 2-sided confidence intervals will be displayed with a 95% confidence level. All tests of interactions between treatment and other factors will be conducted at an alpha level of 0.05. All analyses will follow the intent-to-treat (ITT) principle unless otherwise specified. An ITT analysis is an analysis of data by the groups to which subjects are assigned by random allocation, even if the subject does not take the assigned treatment, does not receive the correct treatment, or otherwise does not follow the protocol.

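### The TRSP band tests are planned at 0.05 with no multiplicity correction: about a 25% chance of at least one false-positive baseline-to-week-24 change if four bands are tested at two sites (assumed correlation 0.5)

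*Combined protocol and SAP*

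**What the plan says.** In SAP section 2.3.4 the TRSP analysis is a single sentence. It plans "dependent t-tests comparing the different frequency bands (alpha, beta, gamma, theta) in the two time points of evaluation (W0 and W24"). The paragraph closes with "significance alpha level test is set up at 0.05", and section 2.3.1 makes tests of treatment effects two-sided at that level unless otherwise noted. No correction is attached to the TRSP tests.

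The TEP step earlier in the same paragraph does have one: "multiple t-tests (corrected with false discovery rate method) at each time point of the TEP waveform".

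Protocol section 1.9 lists the TMS-EEG responses as the eighth secondary efficacy measure and states that "TEPs and TRSP will be computed by stimulating the left and right DLPFC". Section 1.5 makes them a secondary objective: "To evaluate changes from Baseline to Week 24 in the TMS/EEG protocol", with oscillatory activity named among the effects of interest. Section 1.4 expects the TMS-EEG work to contribute to "defining the neurophysiological biomarkers of clinical improvement". No band or site is named as decisive, although the pilot account in section 1.4 describes the increase as most marked in beta and gamma.

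**The concern.** The plan recognises that a set of EEG t-tests needs error control and supplies it for the TEP time-point scan, but not for the oscillation tests made from the same recordings. With no leading band or site, a significant result in any of several band-by-site tests could be reported as a finding on a secondary efficacy measure, and possibly as a candidate biomarker. If nothing changed between baseline and week 24, at least one such result would arise by chance much more often than 5% of the time.

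**Working it through.** **Inputs from the documents.** Four bands and paired tests between W0 and W24 (SAP 2.3.4). Two stimulation sites (protocol 1.9). Two-sided alpha of 0.05 per test (SAP 2.3.1 and 2.3.4). False discovery rate correction attached only to the TEP time-point tests (SAP 2.3.4).

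**Inputs not in the documents.** The correlation ρ between bands and sites, for which I take 0 to 0.8. Also whether the two sites are tested separately, and whether the tests are run by arm. The plan states no error rate for TRSP, so it has no figure of its own to reproduce.

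**Size of the family.** 4 bands × 2 sites = 8 tests in one set of patients. If the sites are combined, 4 tests. If all 8 are run in each arm, 16.

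**Chance of at least one false positive, one set of patients.**
- Independent tests: 1 − 0.95^m. For m = 4, 1 − 0.8145 = 18.5%. For m = 8, 1 − 0.6634 = 33.7%.
- Upper limit under any dependence (Boole): m × 0.05. For m = 8 this is 40%.
- Equal correlation ρ, with c = 1.96: 1 − ∫ φ(z) [Φ((c − √ρ z)/√(1 − ρ)) − Φ((−c − √ρ z)/√(1 − ρ))]^m dz.

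| ρ (assumed) | 8 tests |
|---|---|
| 0 | 33.7% |
| 0.3 | 30.0% |
| 0.5 | 25.0% |
| 0.7 | 19.1% |
| 0.8 | 15.7% |

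For 4 tests at ρ = 0.5 the figure is 15.6%. Simulated paired t-tests with n = 25, in place of the normal approximation, give 34.0%, 25.9% and 16.2% for 8 tests at ρ = 0, 0.5 and 0.8.

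**Both arms tested separately.** The arms are independent, so the chance is 1 − (1 − F8)², where F8 is the 8-test figure.
- ρ = 0: 1 − 0.663² = 56.0%.
- ρ = 0.5: 1 − 0.750² = 43.8%.
- ρ = 0.8: 1 − 0.843² = 28.9%.

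These count placebo-arm results as well as PEA-LUT-arm results.

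**With the correction.** Benjamini-Hochberg at 0.05 over 8 null tests gives a chance of any false positive of 4.9%, 4.3% and 3.3% at ρ = 0, 0.5 and 0.8. Over 16 tests it is 4.9% at ρ = 0 and 4.5% at ρ = 0.5.

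**The case against.** **The number of tests is inferred.** This stands. The TRSP sentence does not say how the two sites enter, and the protocol records from 61 scalp positions without saying how power is summarised over them. The family could be 4, 8 or more. At 4 tests the chance is still about three times 5%.

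**A range of 25% to 44% for four bands at two sites.** A reader might infer this, but the documents do not support it. Eight tests cannot exceed 40%. The 44% needs 16 tests, 8 in each arm, and the TRSP sentence does not specify testing by arm; the wording about each group belongs to the TEP step. The 16-test figure also includes placebo-arm hits, which could not be presented as an effect of PEA-LUT. If only increases were of interest, as the pilot suggests, the independent figure in one arm is 1 − 0.975^8 = 18%.

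**The null is the wrong one for a drug claim.** This stands too. A paired test asks whether power changed from baseline to week 24, and in a progressive disease it may change without any drug effect. The TRSP sentence has no between-group comparison, which is a larger flaw. It does not remove the multiplicity: a group-by-time contrast in 4 bands at 2 sites would still be 8 tests.

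**The TEP comparison is not exact.** The TEP correction covers a scan of many time points used to locate windows, and the model that then compares those windows has no stated correction. So it would be too strong to say that the plan fully controls one EEG analysis and neglects its twin. What remains is that the plan applies false discovery rate control to one set of t-tests in the paragraph and not to the other.

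**Other secondary outcomes are also uncorrected, in a phase IIa trial.** True, and it limits the weight of the point. But TRSP is a listed secondary efficacy measure, is not labelled exploratory, and has several tests inside one outcome.

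**Conclusion.** The concern holds in limited form. As written, the TRSP tests have no multiplicity control. For 8 tests the chance of at least one false-positive W0-W24 change is about 25% at an assumed correlation of 0.5 (34% at 0, 16% at 0.8). For 4 tests it is about 16% to 19% at correlations from 0.5 to 0. If the tests are run in both arms it is about 44% (29% to 56%), with only the PEA-LUT half open to being read as a drug effect. All these figures assume no change in any band; the correlations, the treatment of sites and the by-arm option are my assumptions.

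That no correction will be used is read from silence. It is a fair reading, because the method is named for the neighbouring tests only. A reader might also infer that correcting the p-values would make a significant band evidence for PEA-LUT. It would not, because a within-arm change remains a within-arm change. The point is a worthwhile improvement to a secondary analysis, and the primary FTLD-CDR SoB inference is untouched.

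**What to change.** Add one sentence to the TRSP text in SAP section 2.3.4, for example:

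> All TRSP tests across frequency bands and stimulation sites (and across arms, if run by arm) will be corrected together with the false discovery rate method at 0.05, as for the TEP time-point tests; results significant only before correction will be reported as exploratory.

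The wording avoids a fixed test count because the plan does not define one; the SAP should state how many tests the family contains. Apply the correction to whichever contrast is finally used. It does not stand in for a between-group contrast, which has to be added separately.

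The cost is one SAP sentence and a line of code, using a method that the plan already adopts, and slightly lower sensitivity for a change confined to a single band.

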**SECTION 1.6: INVESTIGATIONAL PLAN**

**Summary of study design**

This is a 24-week, randomized, double-blind, placebo-controlled, Phase 2 study, comparing co-ultramicronized PEA-LUT (GLIALIA, EPITECH group) with placebo for 24 weeks in approximately 50 patients with probable FTD.

Patients will be assigned randomized in a 1:1 ratio to receive Palmythoilethanolamide combined with Lutheoline oral suspension at the dosage of 700 mg+ 70 mg twice every day or placebo for 24 weeks. Participants will be instructed to take two sachets of oral suspension per day (one in the morning and one in the evening). The primary hypothesis being tested is that PEA-LUT will slow global disease progression, the cognitive and functional decline of FTD as compared with placebo.

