**2. STATISTICAL ANALYSIS PLAN**

**2.1. Determination of Sample Size**

The appropriateness of our sample size, i.e. 48 randomly assigned patients (25 to PEA- LUT treatment group and 23 to placebo group), was based on the effect size obtained in a preliminary study by our group using a shorter version of our protocol. Considering the cognitive and behavioural results of this study, we obtained a medium effect size of 0.93 (computed as the difference between the post-treatment and the pre-treatment mean over the pooled standard deviation). With these effect sizes, adopting a two-tailed paired Wilcoxon signed-rank test, with type I error alpha=0.05, the minimum sample for reaching a power (1-β) of 0.95 was estimated equal to n=18 patients per group. We decided to increase our sample size at least of 30% considering possible drop-outs.

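### The only statistical method named for safety is a 0.05-level chi-square test, which with 25 vs 23 patients cannot support a safety conclusion when it is non-significant

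*Combined protocol and SAP*

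**What the plan says.** The last of the secondary objectives in section 1.5 concerns the nature, frequency and severity of adverse events, and its purpose is "to assess the safety and tolerability of PEA-LUT given for up to 24 Weeks". The matching analysis is one sentence near the end of section 2.3.4: "Safety analyses for the treatment period will include comparisons between PEA-LUT group and placebo groups by 2-sided 0.05 significance level Chi-square tests".

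That sentence does not say:
- which adverse event categories are tested;
- whether patients or events are counted;
- which effect measure is reported;
- what is done when expected counts are small;
- how a non-significant result is to be interpreted.

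Section 2.1 gives "48 randomly assigned patients (25 to PEA- LUT treatment group and 23 to placebo group" and bases that number on cognitive and behavioural results of a pilot study. No power or detectable difference is stated for safety. Section 2.3.1 says in general terms that 95% intervals will be displayed, but names no safety quantity. Section 1.9.2.1 covers adverse event recording, vital signs and examinations at clinic visits, and an independent Data Monitoring Committee.

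**The concern.** A significance test answers a useful safety question only if it has a fair chance of detecting an excess worth knowing about. With about 24 patients per arm, it lacks that chance for uncommon and moderately common events. Non-significance is then the expected result even under a substantial excess of harm. If the report contains only p-values, the reader cannot tell whether the data rule out a large excess or simply say little. At stake is the objective itself: the plan as written may yield no quantity from which safety and tolerability can be assessed.

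**Working it through.** **Inputs from the documents.** Two-sided chi-square at 0.05 (section 2.3.4); 25 PEA-LUT and 23 placebo patients (section 2.1).

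**Assumed.** The placebo incidence of an adverse event, varied from 5% to 40%, and all 48 patients evaluable. Fewer evaluable patients would lower the power.

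**1. The plan's own figure.** Section 2.1 says "we obtained a medium effect size of 0.93" and "the minimum sample for reaching a power (1-β) of 0.95 was estimated equal to n=18 patients per group". A paired t calculation with noncentrality 0.93 × √n, and n scaled by the Wilcoxon relative efficiency 3/π, gives power 95.1% at n = 18, so the figure reproduces. The "We decided to increase our sample size at least of 30% considering possible drop-outs" step gives 18 × 1.3 = 23.4, or 24 per arm, which matches 48 in total. This is a within-patient efficacy calculation and says nothing about comparing adverse event proportions between arms.

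**2. Power of the named safety test.** For every table with a of 25 and b of 23 patients affected, compute Pearson's statistic

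X² = N[a(23 − b) − b(25 − a)]² / [25 × 23 × (a + b) × (N − a − b)], N = 48.

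Then sum the two-binomial probabilities of the tables with p ≤ 0.05.

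| Placebo rate | Doubled to | Power | Tripled to | Power |
|---|---|---|---|---|
| 5% | 10% | 8% | 15% | 20% |
| 10% | 20% | 15% | 30% | 42% |
| 15% | 30% | 25% | 45% | 65% |
| 20% | 40% | 34% | 60% | 84% |
| 25% | 50% | 45% | 75% | 96% |
| 30% | 60% | 58% | – | – |
| 40% | 80% | 86% | – | – |

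Power passes 50% at a placebo rate of about 27% for a doubling and about 12% for a tripling. For 80% power, the PEA-LUT rate would have to reach about 36% against 5% on placebo, or 44% against 10%.

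**3. What a non-significant result leaves open.** Take 7/25 (28.0%) vs 2/23 (8.7%). The bracket is 7 × 21 − 2 × 18 = 111, so X² = 48 × 111² / (25 × 23 × 9 × 39) = 2.93 and p = 0.087. The risk difference is 19.3 percentage points, with a Newcombe 95% interval of −3 to +40. With no events among 25 treated patients, the upper limit of the exact two-sided 95% interval is 1 − 0.025^(1/25) = 13.7%.

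**4. Sparse tables.** For 4/25 vs 0/23, the expected numbers of patients with an event are 4 × 25/48 = 2.1 and 4 × 23/48 = 1.9. X² = 48 × (4 × 23)² / (25 × 23 × 4 × 44) = 4.01, so Pearson p = 0.045, while Fisher's exact test gives 0.11. When both arms share the same true rate, the test's actual level is 0.2% at a rate of 2% and 1.8% at 5%. Its maximum over all rates is about 6.0%.

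**The case against.** Three stronger readings are tempting, and the documents support none of them.

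- **That safety is judged by this test alone.** The sentence says the analyses will include chi-square comparisons, the objective is descriptive, and section 1.9.2.1 adds examinations and independent monitoring. This stands. Those provisions concern collection and oversight, however, so chi-square remains the only statistical method named.
- **That a doubling or tripling is usually missed whatever the background rate.** This is not so: 15% vs 45% is detected 65% of the time and 30% vs 60% 58% of the time.
- **That a non-significant result will be reported as proof of safety.** No section says so. The plan only leaves that reading open.

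It can also be said that section 2.3.1 already promises 95% intervals and that a difference of proportions can carry one. That is true, but no safety estimate is named, so the plan commits to none. Low power for adverse events is common to trials of this size, and SAP wording cannot cure it. That is a reason to estimate rather than test; it does not justify leaving the test as the only named method.

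Finally, the sparse-table problem does not run in one direction. The test is conservative for rare events, and the 4 vs 0 example errs towards a false alarm, the cautious side for safety. Replacing it with Fisher's test costs power: 5% vs 15% falls from 20% to 8%, and 10% vs 30% from 42% to 34%. An exact test is therefore no remedy for missed harm.

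**Conclusion.** The point holds as a cheap improvement to the SAP, not as a flaw in design or conduct. The one statistical method named for safety misses a doubling more often than not below about 27% placebo incidence and a tripling below about 12% (about 29% and 14% with Fisher's test). A non-significant result is then compatible with a large excess of harm and cannot by itself support the safety and tolerability objective. These thresholds rest on assumed event rates, since the documents give none, and on all 48 patients being evaluable. For adverse events common enough to exceed the thresholds, the test would detect such an increase more often than it missed it.

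**What to change.** Rewrite the safety sentence in section 2.3.4 as follows.

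- **Main analysis.** For each category (any adverse event, serious adverse event, adverse event leading to discontinuation, and by type), report the number of patients with at least one event per arm and the risk difference with a 95% Newcombe or Miettinen-Nurminen interval. Where an arm has no events, give the exact upper limit.
- **Interpretation.** State that the trial is not powered for safety comparisons and that p > 0.05 is not evidence of safety. Rest the conclusions on the intervals, in particular on the size of excess that the upper limit excludes.
- **Any p-value retained.** Label it descriptive and use an exact method for sparse tables.

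The cost is SAP wording and some extra table columns, with no new data or patients. There are two downsides. The intervals will be wide, so the safety statement will be less favourable than a list of non-significant tests. An exact test also has less power than Pearson's, which is a further reason to base conclusions on the intervals.
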